### Data monitoring

2.8

The institutional review board and Kaohsiung Chang Gung Memorial Hospital's statisticians will be a part of the data monitoring and auditing committee in this study. It is independent from the sponsor and competing interests. Any outcome data will also be collected for participants who discontinue or deviate from intervention protocols. Two study assistance will range checks for data values. The rare but possible side effects of ear acupressure are dizziness, pain, gastrointestinal discomfort, and skin irritation.^[14]^ The small electric flow during Ryodoraku measurement has no influence on human body, and hence will not induce obvious side effect or danger. If adverse events are found during the trial, data and detailed condition will be recorded and analyzed.

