### Participants

2.3

Volunteered participants will be recruited from school teams among junior and senior high schools, and colleges in Kaohsiung, Taiwan through poster announcements in schools with archery club or school team and through internet. The investigator anticipates to enroll 34 participants, 17 each on EA and SA groups. Basic information including training duration of archery (1–3, 3–5, 6–10, and >10 years) and medical history will be collected. Inclusion criteria are healthy archers between 13 and 26 years old, who had been training for >1 year. Exclusion criteria include history of psychiatric disorders or cardiovascular diseases and previous surgical history of dominant hand. Those who are unwilling to provide informed consent will also be excluded. The study procedures and possible risks will be well explained to all the participants.

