### Sample size

2.4

26 participants were estimated to be needed based on repeated-measures analysis of variance with an effect size of 0.48, a significance level (α) of 0.05, and a desired power (1–β) of 0.80. The effect size was calculated from previous literature with G∗power, version 3.1.9.7 (Faul et al, 2020).^[12]^ In the study conducted by Molassiotis et al,^[13]^ the mean (standard deviation) of general fatigue scores at the baseline before the treatment were 16.6 (2.7) at the acupressure group, and 17.8 (2.5) at the sham acupressure group, and the mean (standard deviation) of general fatigue scores after completing the treatment were 14 (2.4) at the acupressure group, and 16.9 (3.0) at the sham acupressure group. Taking the potential 20% drop-outs into account, a total of 34 participants will be recruited.

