### Intervention

2.5

Ear acupressure: Vaccaria seeds are the mature seeds of *Vaccaria segetalis (Neck.) Garcke*, also known as cowherb, and wang-bu-lui-xing in Chinese. It is usually spherical in shape and about 1.5 to 2 mm in size. Vaccaria seeds will be attached by 3 M tape over auricular heart, liver, shen-men, and kidney points, under the application of the Chinese medicine physician who has >7 years of clinical service. Five minutes after administration, participants will start shooting a round of play with 36 arrows (within 40 minutes, including removal of arrows).

Sham acupressure: Same size of 3 M tape as in ear acupressure with a marked black point that looks similar to Vaccaria seed, will be attached over auricular heart, liver, shen-men, and kidney points. Five minutes after administration, participants will start shooting a round of play with 36 arrows (within 40 minutes, including removal of arrows).

Immediately after first round of play, the self-reported questionnaire will be filled out by the participants (V2). After sitting quietly for 15 minutes, the participants will receive Ryodoraku measurement. The Vacciria seeds/sham 3 M tape will be removed and switched to the other intervention (crossover) after the assessments are completed. Archers should rest for 15 minutes (including the time of obtaining written questionnaire and Ryodoraku measurement) between 2 rounds of play according to World Archery Federation rules. Next, the participants will start shooting the second round of play. Immediately after second round of play, the self-reported questionnaire will be filled out by the participants (V3). After sitting quietly for 15 minutes, the Ryodoraku measurement will be performed. Participants could cease the experiment if unbearable discomfort is experienced or unstable vital condition is observed during intervention, or under any personal request to stop the process.

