### Statistical analysis

2.7

All data will be presented as mean ± standard deviation. Chi-square test or Fishers exact test will be applied to compare all patient characteristics and variables at baseline. Repeated measures analysis of variance will be used for comparison of the outcomes between ear and sham acupressures. Statistical significance will be considered at a *P*-value of <.05. All statistical analyses will be performed with SPSS software for Windows, version 25 (Statistics 25, SPSS, IBM Corp., Chicago, IL).

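### The named analysis, repeated measures ANOVA in SPSS, as ordinarily run cannot use the partial records that the plan expects and promises to collect; a mixed model can

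*Protocol article*

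**What the plan says.** All references are to the protocol article.

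- **Analysis (2.7).** "Repeated measures analysis of variance will be used for comparison of the outcomes between ear and sham acupressures". The software is fixed as well: "All statistical analyses will be performed with SPSS software for Windows, version 25". The section names no other treatment comparison and no SPSS procedure.
- **Data after stopping (2.8).** "Any outcome data will also be collected for participants who discontinue or deviate from intervention protocols".
- **Stopping (2.5).** "Participants could cease the experiment if unbearable discomfort is experienced or unstable vital condition is observed during intervention, or under any personal request". V2 follows round 1. The switch of intervention, round 2 and V3 come after it.
- **Size (2.4).** "26 participants were estimated to be needed based on repeated-measures analysis of variance with an effect size of 0.48", with "a significance level (α) of 0.05, and a desired power (1–β) of 0.80". Then: "Taking the potential 20% drop-outs into account, a total of 34 participants will be recruited".
- **Allocation (2.3).** 34 participants, 17 starting on each intervention.

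**The concern.** In a two-period crossover each archer gives one post-intervention value per intervention, V2 and V3. The standard SPSS repeated-measures procedure needs every repeated value and deletes a participant listwise if one is missing. An archer who provides baseline and V2 and then leaves contributes nothing, although the V2 value was collected and 2.8 shows that such data are wanted.

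The plan itself expects incomplete records, at 20%. The method it has fixed is therefore a poor match for its own drop-out figure and its own collection rule.

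What is at stake is bias. If the chance of a missing V3 depends on how the archer responded at V2, completers are a selected group and their within-person difference need not equal the effect in all who were allocated. The self-reported fatigue and attention scales are primary outcomes, and a participant may leave because of how they feel, so such dependence is plausible. It is not established.

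**Working it through.** **1. The plan's own size.** Inputs from 2.4: effect size 0.48 (taken as Cohen's f), α 0.05, power 0.80. Assumed, because not stated: between-factors test, 2 groups, m = 3 measurements, correlation ρ = 0.5. With noncentrality N·f²·m / (1 + (m − 1)ρ), the smallest even N reaching 0.80 is 26, with power 0.82. This matches the plan.

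Drop-out: 26 / (1 − 0.20) = 32.5, so 33, or 34 for equal groups. This also matches.

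**2. Power after listwise loss.** 34 × 0.80 = 27.2, so about 27 complete records and about 7 incomplete. 27 exceeds 26. Under the assumptions of step 1, power is 0.835 with 27 and 0.914 with 34. The recruitment target already pays for a completers-only analysis.

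**3. How bias can arise.** Assumed inputs, none from the document: outcomes with SD 1, higher is worse, no true effect, no carryover, 17 per sequence, within-person correlation ρ. Suppose the k archers with the worst V2 in the ear-acupressure-first sequence give no V3, and everyone else is complete. The completers-only estimate of ear minus sham is

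½ × [mean difference in ear-first completers + mean difference in sham-first archers].

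The second term averages 0. If the ear-first completers' mean V2 is −c, their expected V3 is −ρc, so the bias is −½(1 − ρ)c. For k = 7 of 17, c is about 0.66. At ρ = 0.5 the bias is −0.5 × 0.5 × 0.66 = −0.165. Simulation gives:

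| Leavers, all ear-first, worst V2 | ρ = 0.3 | ρ = 0.5 | ρ = 0.7 |
|---|---|---|---|
| 7 | −0.23 | −0.16 | −0.10 |
| 4 | −0.13 | −0.10 | −0.06 |
| 2 | −0.07 | −0.05 | −0.03 |
| 1 | not tabulated | −0.03 | not tabulated |

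Negative values favour ear acupressure.

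**4. Other equally admissible assumptions.** Take ρ = 0.5 and let the 7 worst V2 scorers leave from both sequences together.

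- No true effect: bias about 0.
- True benefit of 0.5 SD: the completers-only estimate averages about 0.45. The sham-first sequence loses more of its poor scorers, and the benefit is understated.
- Missing at random, 20%: completers-only and mixed-model estimates both average about 0.50 for a true 0.50.

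**5. What a likelihood analysis does.** In the settings of step 3 with 4 or 7 leavers, using every V2 value by likelihood leaves a bias of at most 0.006 SD, with an equal or slightly smaller standard error. In a pooled-loss run with true effect 0.5, a mixed model with intervention and period averaged 0.49 against 0.44 for completers. Its standard deviation was slightly larger there (0.202 against 0.184). The near-zero bias in the first case is partly built in, because loss was made to depend only on the observed V2 and the true correlation was supplied.

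**The case against.** The strongest reply is that 2.7 states no deletion rule. Listwise deletion is a property of the usual SPSS procedure, SPSS 25 also offers MIXED, and analysis sets and missing-data handling may sit in a fuller document that is not shown. That is right as far as it goes, and the absence of those details is not the point here. The point is that the article does fix a method, and that method in its ordinary meaning cannot take incomplete records.

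Two stronger readings are tempting, and the document supports neither.

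- **That the result would cover only archers who tolerated both tapes.** Deletion follows a missing measurement, not intolerance. Someone who removes a tape or deviates but is still measured at V3, as 2.8 intends, has a complete record and stays in. Section 2.5 does not tie removing a tape to leaving before V2, and it also allows stopping on personal request for any reason.
- **That the bias favours ear acupressure.** This needs one-sided loss of the worst ear-first scorers. Section 2.8 calls the side effects of ear acupressure rare, the 20% in 2.4 is a general allowance over both sequences, and the first tape comes off at the switch anyway. With one such leaver the bias is 0.03 SD. With pooled loss it is nil, or against ear acupressure when there is a true benefit.

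It is also fair to say that an archer who leaves before V2 has no post-intervention value, so neither method recovers anything for that person.

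**Conclusion.** The point holds in a limited form. The named ANOVA, run in the usual way, discards participants with V2 but no V3, in a plan that expects 20% drop-outs and undertakes to collect data from those who stop. The estimate can then be biased if missing V3 depends on the V2 response.

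Neither size nor direction can be asserted. The scenarios run from about 0 to 0.23 SD. The upper end requires all 7 losses to be the worst scorers in one sequence, with a within-person correlation of 0.3. All of this rests on assumed drop-out patterns and correlations.

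Power is not affected in any way that matters to the plan's own target (27 against 26). The change is worth making because it is cheap and the same software does it, not because a large bias has been shown.

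**What to change.** 1. **Section 2.7.** Replace repeated measures ANOVA by a linear mixed model (SPSS MIXED) with fixed effects for intervention, period and sequence and a random participant effect. Fit it to all collected V2 and V3 values, including those of participants with only one of them, by the intervention assigned for that round. Report the completers-only analysis as a sensitivity analysis.
2. **Sections 2.5 and 2.8.** Reconcile the wording on stopping with the wording on continued data collection, so that it is clear which measurements are still sought from someone who stops an intervention but agrees to be measured. Who should stop, and when, is for the investigators and is not addressed here.
3. **Case report form.** Record which tape was worn, and the time and reason for stopping.

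Cost: one sentence in 2.7, one clarifying sentence in 2.5 or 2.8, and one field on the form. No added participants, visits or software. The downside is small: the model assumes that missingness depends only on observed values, so it does not protect against loss driven by unrecorded discomfort, and it recovers nothing for those who leave before V2.

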## Discussion

3

The ANS is a control system of human body that regulate physiological activities and internal organ functions to face the fight-or-flight response. It is delicate, complicated, and it involves body movements and emotion. The HRV is a non-invasive and reliable method to assess the activity of ANS. By monitoring the change in HRV, it is possible to analyze the ANS condition during archery contest. Based on previous literature, we could conclude that the activation of parasympathetic nervous system is the key point in improving archery performance. It is important to find an intervention that is easy to perform, less irritating, and non-pharmacological (no risk of doping). Traditional Chinese medicine has been incorporated in sports medicine in recent years. Acupuncture focusses on the characters of treating from distant parts and regulating the entire body function. Ear acupressure possesses the advantages of being convenient, immediate, non-invasive, and less irritative.

How acupuncture affect the ANS and HRV had been discussed in a systematic review by Lee et al.^[15]^ Publications until October 2009 had been searched on 14 databases without language restrictions. Twelve randomized control trials met the inclusion criteria and had been included. The risk of bias in each study was assessed using the Cochrane criteria. Five randomized control trials revealed significant differences in HRV between patients treated with acupuncture compared with those with sham acupuncture (control group). However, most other randomized controlled trials showed inconsistent results or no significant HRV differences between subjects with acupuncture treatment and sham acupuncture. The review concluded that sham-controlled randomized controlled trials showed variable results and no clear evidence about the specific effect of acupuncture on HRV. Further research is imperative.

Non-invasive auricular stimulation (ear acupressure) was found to affect both meridian activities and HRV in middle-aged women in weight reduction.^[16]^ In post-caesarean section women, those who received ear acupressure had significantly lower heart rate, and anxiety and fatigue symptoms than women with usual care at 5 days postpartum.^[17]^ In a study involving 14 healthy volunteers, significant heart rate decrease and HRV total increase were observed during ear acupressure and/or ear acupressure vibration over auricular heart point.^[18]^

In this study protocol, we will perform ear acupressure with Vaccaria seeds and sham acupressure in both groups of participants in a crossover design. The preceding test had confirmed the similarity of Vaccaria seeds and black mark on 3 M tape to assure the completion of blinding. The immersive course and the setting protocol of this experiment could mimic the actual change of mental and physical status during competitions. The outcome evaluation will include change of meridian activities and balance index with Ryodoraku device, HRV with continuous heart rate recording, motion stability with WIMU, attention and fatigue levels with self-reported questionnaires, and the scores of the 2 sections as the performance. In conclusion, we hypothesized that ear acupressure could cause immediate effect of modulating the ANS and meridian activities, and consequently improve archery performance.
